## **9. Procedure**

### **9.1 Investigator meeting**

Before the study is initiated, the investigators, therapists and psychiatric nurses involved in the study will meet and be briefed about the protocol. If impossible to meet face-to-face there will be arranged an online meeting. The meeting will be logged.

### **9.2 Training course in Good Clinical Practice**

Before initiating the study, all participant researchers have to complete a certification-course in Good Clinical Practice (GCP).

### **9.3 Recruitment of participants**

Since relapsed OCD-patients are not necessarily actively seeking treatment, the trial will be announced in the local papers and on web-sites relevant for OCD-patients. The announcement will inform the patients to contact the OCD-team for further information regarding the referral procedures. Eligible patients will also be referred to the OCD-team by their local psychiatric outpatient clinic. Patients previously treated in an OCD-team will also be informed of the trial. The OCD-teams websites will also feature information about the trial, as well as information on how to get in contact with the investigators.

### **9.4 Inclusion of participants**

- All patients referred to an OCD-team, provided that they previously have received OCD-treatment, are screened by a local therapist for inclusion, including Y-BOCS and M.I.N.I interviews.
- If patients fulfil inclusion criteria, they will watch a video presenting the study and receive written information before informed consent is signed.
- Before the informed consent is signed, the relevant information regarding previous treatment-course is collected (e.g Y-BOCS scores)
- The information is presented to the national team of assessors, and decision regarding inclusion is made.
- Each patient will receive information about the decision, as well as practical details regarding appointments, procedures, treatment and follow-up.

### **9.5 Preparation for treatment**

- After inclusion and before treatment, a local OCD therapist conduct an intake interview (anamnestic information and information regarding previous treatment and timeline for relapse), and information regarding the cET is briefly repeated before treatment credibility (CT) is measured.
- The SCID-5 and Y-BOCS are performed within 4 weeks prior to the intervention, by independent and specially trained assessors. For training procedures, see section 8.4.
- The patient fill out relevant self-report questionnaires (see Table 1)

### **9.6 Treatment**

- **Day 1 Psycho-education and treatment preparation (3 h)**

Participants receive psychoeducation focused on the rationale behind the cET treatment which emphasizes the differences between this approach and the ERP they previously have received. Relevant exposure tasks will be decided upon. The patients are introduced to the micro-intervention “Leaning into the anxiety” (LET), which is to be practiced throughout the two days of exposure

- **Day 2 (8 hrs) and 3(8 h + 2 h psychoeducation for family): Therapist assisted Exposure and response prevention combined with DCS/ placebo**

Patients will engage in individually tailored and therapist assisted ERP, using the micro-intervention LET. Exposures will be conducted in a variety of settings with high ecological relevance, most of them out of the office. DCS on day 2 (first day of exposure) will be taken after 3 hours of the cET. DCS on day 3 will be given approximately 1 hour before the first exposure session of the day.

On day 3 the patient’s family/ significant others are invited to a 2 h psychoeducation.

- **Day 4: Summarizing and relapse prevention**

Summarizing (“lessons learnt”) and planning self-exposures for the next three weeks. Focus will be on teaching the patients how to be “their own therapists. The patients are provided with written information covering procedures and times for upcoming assessments. The patients will, in a group setting, give structured feedback/ evaluation of the treatment at the end, and will prepare exposure tasks to be performed the first three weeks after the treatment.

### **9.7 Homework assignments during the first three weeks post treatment**

Participants will log their compliance to the home-work on a daily basis and return the logs to the clinic weekly online or by mail in pre-paid envelopes with return address.

### **9.8 Follow-up visit to the clinic**

There will be scheduled an individual follow-up meeting at the clinic three months after the 4-day treatment is completed.

### **9.9 Post-treatment assessments**

*After one week (T1)*

**Y-BOCS interview and self-report questionnaires** (see table 1).

*After 3 and 12 months and 5 years.*

SCID-I (at 3 months only OCD module) and Y-BOCS interviews by specially trained assessors as well as a number of self-report instruments (see table 1).

## **10. DCS/ placebo side effects**

The DCS will be administrated in two single dosages, and the patients will be randomized to receive either 100 mg or 250 mg. Both dosages are smaller than standard dosage when the drug is administrated for its original purpose.

Previous trials with DCS with doses of 25-250 mg have reported little or no side-effects of DCS compared to placebo (11, 117-119). One potential danger could be that DCS would produce

reversed effects, i.e. DCS could enhance fear learning instead of fear extinction. One study reported facilitation of reconsolidation of fear if DCS was given prior to a single recall trial, but after using several recall trials, it facilitated extinction (120). No other published reports have reported any reversed effects of DCS.

In order to control for possible interactions with antidepressants (121) patients will be stratified in accordance to whether they receive antidepressants or not.

The DCS will be taken at the clinic, administered by a designated person, and the patients will be together with the therapist for at least five hours after intake. This ensures both compliance as well as the possibility to record side effects. Patients will be in contact with the clinic weekly for the first three weeks after the DCS/placebo intervention, which further ensures recording of side effects.

## 11. Measures to minimize bias

The following procedures have been taken to avoid bias:

- This is a double-blind study and the study capsules will be of identical appearance in order to protect the blinding for both participants, therapists, assessors and investigators. As there are no obvious side effects associated with the drug, the placebo capsules will be passive.
- Post-treatment assessments of primary outcomes are conducted by specially trained assessors who are blinded to the treatment conditions and not involved in the treatment (see section 8.4).

### 11.1 Packaging, Labeling, Storage and Handling of Investigational Medicinal Products

|             | ERP                              | DCS 250 mg                         | DCS 100 mg                         | Placebo                            |
|-------------|----------------------------------|------------------------------------|------------------------------------|------------------------------------|
| Dosage form | Concentrated, therapist assisted | Capsule DCS 250 mg                 | Capsule DCS 100 mg                 | Placebo capsule                    |
| Unit dosage | 4 days                           | 250 mg a day, two consecutive days | 100 mg a day, two consecutive days | 250 mg a day, two consecutive days |

### 11.2 Treatment Assignment/ Randomization

Patients are upon inclusion randomly assigned to DCS or placebo using a 2:2:1 ratio of 250 mg DCS: 100 mg DCS: placebo. In order to control for potential interaction effects with antidepressants (121), patients will be stratified on current anti-depressive medication or not. Within each subgroup patients will be randomized in blocks of 5 into ERP+DCS 100 mg, ERP+DCS 250 mg, or ERP + Placebo in the proportions 2:2:1.

A research unit at Karolinska Institute, Sweden, which is not involved in the study, will be responsible for the randomization. Randomization lists will be sent directly to Kragerø pharmacy that will be responsible for providing the medication for patients enrolled.

### **11.3 Blinding and code breaking**

Sealed envelopes with the DCS/Placebo treatments will be sent from the Kragerø Tablet Production and given to the medical competent. The envelopes will be kept in a secured place and accessible to any person authorized to un-blind. A decoding list containing the treatment codes will be kept.

The code for any study participant should only be broken by the medical competent or authorized person if it is absolutely necessary to ascertain the type of treatment given. The circumstances under which the code may be broken are life-threatening emergencies, for which the choice of therapy may depend on the treatment received by the patient. If so, the medical competent must write his/ her name, signature, date, the number of the participant concerned and reason for breaking the code on the code envelope. All information concerning adverse drug reactions, drug interactions are given in the SPC [66]. The blinding will be broken after the 12 months follow-up. At the 5-year follow-up the assessors will be blinded for the randomization.

### **11.4 Concomitant and prior medication**

The patients are not allowed to use anxiety reducing medication (barbiturates, benzodiazepines, alcohol) in the treatment period (during the two active exposure days). There are no restrictions on the use of dietary supplements or herbal medicines.

### **11.5 Compliance to drug treatment**

DCS/ placebo will be administered by designated personnel in order to ensure compliance, and the drug will be taken in front of the therapist.

### **11.6 Product Accountability**

Both DCS and placebo will be supplied from Kragerø Tablet Production AS, [name]. [contact]. Treatment management will be under responsibility of the investigator.

The therapeutic DCS units and placebo will be sent to the sites and will be stored in a secure area with restricted access. The expiry date will appear on each box and each label. Placebos are labeled same expiry date as the DCS. Name and phone number of the principal investigator will also appear on the label.

The investigators will acknowledge the receipt of therapeutic units by signing the shipping form. The DCS treatments will be dispensed by the investigators in accordance with the study plan and following dispensing methods described below. Drug accountability will be the responsibility of the investigator. Remaining capsules will be collected by monitor and sent Kragerø Tablet Production AS for destruction.

### **11.7 Continuation of cET-Treatment in discontinuation of DCS-treatment**

If a participant decides not to take the DCS/placebo treatment Day 2, he/she has still the opportunity to continue the concentrated ERP treatment, but the patient will be excluded from the study. The whole trial will end when the last subject has completed the 12-month follow-up telephone assessment (separate papers describing the short- and long-term effects of DCS will be written). A 5 year follow-up telephone assessment will be conducted and data will be collected and analyzed separately.

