## 5. Inclusion and exclusion criteria, withdrawal

All 15 OCD-teams in Norway refer patients to the study, thus providing nationwide coverage of relapsed or non-responsive OCD patients.

A maximum of 160 patients will be included (see p.31 for power calculations) within the period from October 2015- June 2018.

Through the National OCD-implementation project all OCD-patients in Norway are ensured access to evidence based treatment. Standardized procedures for collection and storage of data (quality databases) are also established. These data will serve as reference data for standard treatment response, as well as provide detailed information regarding the first treatment-course for the relapsed OCD-patients.

The inclusion procedure implies that all relevant patients in Norway in the given time period will be offered participation. If this population turns out to be fewer than 160 patients during the study period, the inclusion period might be extended six months. If less than 160 patients are included at that point, analyses will be performed on the number of patients included by the end of the study period.

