### **5.4 Subject Log**

If possible, the investigator must record the reason and the exact time of the premature discontinuation of treatment in the case report form (CRF). If more than one reason is given, the investigator must indicate the main reason.

In case of treatment discontinuation for any reason between visits T0 and T2, an end-of-study visit should be done with all the assessments planned for the follow up as early as possible after the treatment study discontinuation.

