## 13. Statistics and Data Management

### 13.1 Statistical Analysis

Statistical analysis will be performed by the investigator and specially designated collaborators and quality controlled and cross-checked by independent party

The primary objective is to demonstrate superiority of concentrated ERP + DCS vs. concentrated ERP + placebo at significance level of  $< 0.05$  (5%). Data will basically be analyzed using intention to treat methodology with a mixed models design, accounting for missing data, with relevant covariates for a given analysis. Data will primarily be analyzed employing multivariate methods (ANOVAs/MANOVAs) with repeated measurement.

Covariates are described in the moderator section (Chapter 6.5). Missing data will be replaced (multiple imputation methods). There will be calculations of effect sizes (Cohen's effect size) for all primary and secondary endpoints. Other relevant multivariate statistical analyses will be performed if relevant to elucidate results of importance to the objectives of the study. Safety data (e.g. side effects) will be collected and summarized in the study results.

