### 13.2 Determination of Sample Size

A meta-analysis by Norberg, Krystal & Tolin [69] found a medium effect size for ERP + DCS for heterogeneous samples of OCD-patients. However, in the current study, only patients who have relapsed after an initially successful ERP-treatment will be included. This is a sample which supposedly increases the possibility to detect DCS-effects and we assume that the effect size would be larger than that found in previous studies. In order to have 80% power to detect a moderate effect size ( $d = 0.50$ ) at an alpha-level of 0.05 a total of 160 patients will be included (64 in each of the DCS-conditions and 32 in the Placebo group). Patients lost or withdrawing from the study will be treated as drop-outs and replaced. We estimate an increased sample size of 10 patients, in total, to compensate for possible drop-outs.

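### Randomised patients are excluded from the study or replaced after randomisation, which conflicts with the stated intention-to-treat analysis, and the planned total is inconsistent (160 or 170)

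*Protocol*

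**What the plan says.** Section 11.2 sets the time of allocation: "Patients are upon inclusion randomly assigned to DCS or placebo", in the ratio 2:2:1. Section 9.5 places the baseline Y-BOCS and SCID interviews after inclusion. Section 8.6 places the first capsule on Day 2, after three hours of exposure treatment.

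Three rules then act on patients who are already randomised:

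- **Section 11.7.** A patient may refuse the Day 2 capsule; then "he/she has still the opportunity to continue the concentrated ERP treatment, but the patient will be excluded from the study".
- **Section 5.3.** Patients with high suicide risk, or a suicide attempt during the two dosing days, are excluded from the study.
- **Section 13.2.** "Patients lost or withdrawing from the study will be treated as drop-outs and replaced".

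Section 13.1 states the analysis principle: "Data will basically be analyzed using intention to treat methodology with a mixed models design, accounting for missing data". It adds multiple imputation for missing data.

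Two passages lean towards keeping patients. Section 5.4 says that after discontinuation of treatment between T0 and T2 "an end-of-study visit should be done with all the assessments planned for the follow up as early as possible". Section 11.8 says that patients whose condition worsens stay in the protocol.

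On numbers, section 5 says "A maximum of 160 patients will be included". Section 13.2 plans 160 (64, 64 and 32) and estimates 10 more to cover drop-outs.

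**The concern.** Intention to treat means that every randomised patient is followed and analysed in the assigned arm. A rule that takes a randomised patient out of the study, or puts a new patient in the place of one who was lost, does the opposite. If the rules are followed as written, the outcomes of those patients may never be collected.

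An analysis plan can define analysis sets and imputation models, but it cannot recover assessments that were not made. That is why the point belongs in the protocol and should not be left to a later document.

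Timing adds to the concern. The hypothesis in section 3 expects the arms to separate at follow-up. The expectation of very low drop-out in section 13.1 rests on experience of the intensive treatment days only. The losses that matter most are therefore the ones the protocol has least basis to call rare.

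**Working it through.** **Step 1. Order of events.** Inclusion and randomisation (11.2) come first. Baseline interviews within four weeks before the intervention (9.5) follow, then Day 2 and the first capsule (8.6), the second capsule on Day 3, and T1 to T3. All three removal rules act after randomisation. They differ in how likely they are to differ by arm:

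| Rule | When it acts | Could it depend on the arm? |
|---|---|---|
| 11.7, refusal of Day 2 capsule | Before any dose, identical capsules, blinded | Unlikely |
| 5.3, suicide risk or attempt | On the dosing days, possibly after a dose | Possible |
| 13.2, loss or withdrawal | Any time, including after both doses | Possible |

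**Step 2. The plan's own totals.** 64 + 64 + 32 = 160. Adding 10 gives 170, or 68, 68 and 34 at 2:2:1. The allowance is 10/170 = 5.9% of those randomised, and 160/(1 − 10/170) = 170, so the 10 is consistent with section 13.2 itself. It is not consistent with the maximum of 160 in section 5.

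**Step 3. Size of the bias, modest imbalance.** Bias = outcome gap × difference between arms in the share removed. Assumptions, none from the protocol: removed patients would score 5 Y-BOCS points worse at 12 months, the SD is 6, and the share removed differs by 5 to 10 percentage points.

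- 5 × 0.05 = 0.25 points; 0.25/6 = 0.04 SD
- 5 × 0.10 = 0.50 points; 0.50/6 = 0.08 SD

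The upper figure is about one sixth of the planned d = 0.50.

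**Step 4. Size of the bias, ten patients removed and replaced.** Assumptions: true effect zero, removed patients 0.5 to 1.0 SD worse than those retained, and both DCS arms pooled, so that 128 v 32 are analysed two-sided at 0.05. The standard error of the difference is √(1/128 + 1/32) = 0.198 SD. With bias b, the type I error is 1 − Φ(1.96 − |b|/0.198) + Φ(−1.96 − |b|/0.198).

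| Where the ten fall | Share removed, DCS v placebo | Size of b (SD) | Type I error |
|---|---|---|---|
| Balanced (8 and 2) | 8/136 v 2/34, both 5.9% | 0 | 0.05 |
| All DCS | 10/138 = 7.2% v 0 | 0.04 to 0.07 | 0.054 to 0.066 |
| All placebo | 0 v 10/42 = 23.8% | 0.12 to 0.24 | 0.09 to 0.23 |

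Removing the worse patients flatters the arm that loses them. Losses concentrated in placebo would therefore work against DCS, and losses concentrated in DCS would work in its favour.

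**The case against.** The strongest reply is that the protocol keeps more patients than these rules suggest. Section 11.7 covers only refusal of the Day 2 capsule, blinded and before any dose. Leaving such patients out resembles a modified intention-to-treat set and should not differ by arm. Section 11.8 keeps patients who worsen, section 5.4 obtains an assessment after discontinuation, and section 13.1 prescribes methods for missing data that would have little purpose if everyone lost were deleted. This stands as far as the capsule refusal goes. It does not settle the matter, because the protocol defines no modified set and nowhere says that excluded or replaced patients stay in the analysis. The mitigating passages show that the instructions pull in opposite directions.

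A reader might also infer more than the text supports:

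- **That the analysis will be a completer sample.** This holds only if replaced patients leave the analysis, which section 13.2 implies but does not say.
- **That the visit in section 5.4 takes the place of the scheduled follow-ups.** The section does not say so. It is silent on whether T1 to T3 continue.
- **That replacement is impossible for losses at 12 months.** Enrolment runs from October 2015 to June 2018, with a possible six-month extension if 160 is not reached. Patients enrolled up to about June 2017 reach 12 months while it is open, so the difficulty concerns later enrolees only.
- **That replacement contradicts the extra 10 in the same paragraph.** The 10 can be read as the replacement pool. The conflict is with the cap in section 5.
- **That the rules cost power.** With replacement the analysed number does not fall, so loss of power is not the harm here.

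**Conclusion.** The conflict holds and rests on the text, not on a calculation. Sections 5.3, 11.7 and 13.2 remove or replace randomised patients, section 13.1 promises intention to treat, and sections 5 and 13.2 give totals that cannot both apply. Replacement of patients lost after dosing and the section 5.3 exclusion matter more than the capsule refusal.

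The numerical effect is probably small. It is nil under balanced loss and 0.04 to 0.08 SD under the assumptions of step 3. It reaches 0.12 to 0.24 SD only in the extreme case of step 4, where all ten losses fall in the small placebo arm. The outcome gaps, the SD and the imbalances are assumptions, because the protocol gives no figures for them. What makes the point worth fixing despite the small expected size is that outcomes not collected cannot be recovered, and the repair is cheap.

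**What to change.** Reconcile sections 5, 5.3, 5.4, 11.7, 13.1 and 13.2 as follows:

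1. State that every randomised patient stays in the scheduled T1 to T3 assessments, whether or not capsules were taken or treatment was stopped, unless consent is withdrawn, and is analysed in the assigned arm.
2. Remove the exclusion from the study in sections 11.7 and 5.3 as far as follow-up and analysis are concerned. Decisions to stop study drug or treatment stay with the investigators and are not touched.
3. State in section 5.4 that the end-of-study visit does not end the scheduled assessments.
4. Delete the replacement rule in section 13.2.
5. Give one planned total in sections 5 and 13.2: 160, or 170 if the allowance of 10 is kept.

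Cost: protocol wording, plus blinded interviews, the three-month visit and questionnaires for a few more patients. There is also slight dilution from patients who took no drug. If a share q gets no drug effect, d becomes 0.50 × (1 − q). With 170 randomised and all analysed (136 v 34 pooled, two-sided t test), power is 0.737 at q = 0, 0.711 at q = 3% and 0.685 at q = 5.9%. The last figure is a high case, because it assumes that the whole allowance of 10 took no drug. That the starting value is below 80% is a separate sample-size matter.

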### **11.8 Unscheduled visits to the clinic**

All patients included will be receiving what is part of standard care in the OCD-team. If the OCD should be worsened, or if any other psychiatric problems should arise or be worsened (e.g.

depression) the patients will have the option to contact the OCD team, and the patients will receive the necessary care. Such patients will not be removed from the protocol, but be thoroughly described in the published article of the outcome study.

